#### Community based exercise programme (FaME)

The FaME programme comprises one hour-long PSI-delivered group exercise class in a local community centre for a maximum of 15 participants, and two 30 minute home exercise sessions (based on the OEP) per week for 24 weeks. Participants will be advised to walk at least twice per week for up to 30 minutes at a moderate pace. The programme includes leg muscle strengthening and balance retraining that progress in difficulty. Progressive trunk and arm muscle strengthening, bone loading, endurance (including walking) and flexibility training, functional floor skills (see below) and adapted Tai Chi complete the evidence based programme. Ankle cuff weights, Therabands (elastic resistance training bands) and mats are also used throughout the programme. The group exercises include retraining of the ability to get up from the floor and floor exercises to improve strength, balance and coping strategies to reduce the risk of complications resulting from a long lie [34].

The delivery of the FaME programme will be standardised through training of PSIs before the trial starts and there will be regular quality assurance visits for the FaME classes to check delivery protocols are being followed.

The PSI will keep a register of attendance and record tailoring of the programme and any feedback from participants. They will follow up non-attenders by telephone as necessary, recording any positive or negative feedback, and notify the research team about reasons for non-attendance or drop-out. Participants will be given a booklet containing their home exercise instructions.

FaME groups will contain 9 or 10 participants, so there will be 4 or 5 classes per week for each of the practices allocated to this arm. The number of PSIs running these classes will be determined by their availability, but the aim is to maximise continuity and standardisation in physical activity training, so the ideal would be to have one PSI who would lead all groups in one practice. This may be difficult to achieve, but we will report the actual deployment of PSIs in our findings. The same applies to peer mentors for OEP classes

General practitioners in participating practices allocated to either the FAME or OEP programmes will be discouraged from referring participants involved in the trial to other exercise therapy projects, outside the study.

#### Usual care

Participants in the usual care arm will not be offered either the OEP or FAME programmes. They will be free to participate in any other exercise as they would if they were not participating in the trial.

#### Cultural and ethnic sensitivity

Cultural and religious requirements will be accommodated within the exercise programmes. The recommendations from the Help the Aged Minority Ethnic Elders Falls Prevention Programme (MEEFP:http://www.helptheaged.org.uk/meefp) will be followed and the research team will liaise closely with Skills Active (Sector Skills Council for Active Leisure and Learning), who are working with the Integrated Fitness Initiative's (IFI) current programme: Physical Activity Provision for Ethnic Minority Groups. In particular the FaME group classes will ensure that recommendations for attire will respect cultural, religious beliefs and customs for a range of ethnic groups. Single sex exercise groups will be scheduled as required, and separate changing facilities and gender specific instructors will be provided wherever possible. Windows in the exercise classrooms will be screened as appropriate. Family support will be encouraged, and classes will be provided at different times of the day The OEP programme will respect participant's preferences regarding family support and participation in the home exercise programme.

All research material and exercise manuals will use a maximum reading age of 9 years. Inability to read the material is not a formal exclusion criterion as the individual may be able to follow movement and correction accurately in classes and family members will be allowed to act as interpreters. Where possible, translations of research material and exercise manuals will be provided.

### Outcome measures

The primary and secondary outcome measures have been chosen to reflect the needs of participants (e.g. functional outcomes, falls, confidence, quality of life, participant costs), of commissioners of exercise services in primary care and policy makers (e.g. physical activity, falls, NHS costs).

The primary outcome will be the proportion reaching the recommended physical activity (PA) target of at least 30 minutes of activity of moderate intensity on at least 5 days each week, measured using the CHAMPS, PASE and PHONE_FITT questionnaires. While measures will be taken at 0, 6, 12, 18 and 24 months after the intervention, our primary analysis will be of 12 month data, as this is the time when the effect of the intervention is expected to be maximal, as seen in a previous evaluation of the OEP in New Zealand [37].

The secondary outcomes will include:

(1) The direct health benefits: i.e. functional and psychological status, the rate of falls (the major safety outcome measure), the number and nature of falls, and fear of falling,

(2) Stage of change, self-efficacy for exercise and physical self-perception (self-esteem relative to the physical domain), which includes measurement of perceived importance (the degree to which participants value their physical condition, body image and physical strength) to inform predictors of exercise adherence and continuation, and participants' judgement of the value or importance of physical activity,

(3) Health - related quality of life and Quality adjusted life years (QALYs) [38],

(4) The NHS and private (participant) costs of each exercise programme, and possible cost offsets, identified from a comparison of health and social service utilisation of participants in all groups during the study period.

#### Ascertainment of outcomes

The following functional assessments will be used by researchers at baseline and at the end of the interventions (and at 6 months after allocation in the usual care arm):

1. Modified Clinical Romberg Static Balance test, eyes open and closed [39].

2. Timed get-up and go (with and without distraction) (TUG) as a measure of balance and falls risk [40].

3. Functional Reach as a measure of balance and falls risk [41].

4. 30 second chair rise as a measure of lower limb strength and power [42].

The following validated tools will be used at baseline, and as self-completion questionnaires at follow-up:

1. Confidence in balance measured by the ConfBal scale [43]. A total score is provided as a measure of confidence.

2. Confidence in carrying out a range of basic activities of daily living without falling measured by the Falls Efficacy Scale-International (FES-I) [44].

3. Readiness to change measured by the transtheoretical model [45] and applying it to exercise behaviour to determine perceived barriers [46] and self efficacy for exercise [47].

4. Quality of life will be measured using Older People's QoL Questionnaire (OPQOL) [48-50]

5. Social network size and density will be measured using the brief Lubben Social Network scale [51] and perceived social support measured by the Multidimensional Scale of Perceived Social Support (MSPSS) [52].

6. Subjective Habitual Physical Activity will be assessed using a number of validated questionnaires to ensure all domains of activity and sport are considered, including the Phone-FITT, PASE and CHAMPS [53-55] and the current level of activity questions used in the Household Survey [56].

7. Attitudes and beliefs about falls prevention interventions will be measured using the AFRIS questionnaire [57].

8. Falls risk will be measured by the Falls Risk Assessment Tool (FRAT) [58].

9. Health- related quality of life will be measured by the SF-12 [59]. Quality Adjusted Life Years (QALYs), which are the main outcome for the economic analysis, will be based on EQ-5D utility weights obtained by transforming SF-12 scores [38].

In addition, demographic information, co-morbidity, medication, use of general practice and hospital and community social services will also be recorded at baseline and updated at subsequent assessments. Falls will be ascertained by self-completed fall diaries, with follow up of non-responders and telephone contact with fallers to ascertain the type of fall and any injury and health care usage that resulted.

Feedback will be sought from all exercise participants using a questionnaire which will include open questions eliciting views of the programme, reasons for drop-out, barriers to attendance and self perceptions of the benefits and disadvantages of the programmes to aid future implementation.

For the purposes of the economic analysis, the resources used in the delivery of the interventions will be collected from records kept by PSI instructors (FaME) and the research staff and peer mentors (OEP). The use of facilities and equipment, and the time spent on travel and instruction will be included and monetary costs will be assigned according to market rates.

In addition, the use of health and social care services (GP, community, outpatient, hospital admission) will be recorded for participants in all groups by means of the falls diaries. Self reported service utilisation will be verified from the primary care medical records of consenting patients after the follow up period. Costs of services will be obtained from local and national sources [60]. Health and social care costs in the exercise groups will be compared with each other and with the usual care (no exercise) group to assess the extent to which the costs of the exercise intervention may be offset by savings elsewhere in the health and social care system.

No other encouragement to continue with physical activity will be given to participants, and all potential reinforcements in the form of diaries and six monthly contracts will be given to all three arms of the trial.

#### Baseline data collection

Baseline assessment will include all functional assessments plus administration of all questionnaires described above.

#### Follow-up data collection

Follow up assessments occur at 24 weeks after the commencement of the intervention, and at 6, 12, 18 and 24 months after the completion of the intervention for participants in both intervention arms, and at 24 weeks after randomisation and at 6, 12, 18 and 24 months after completion of the 24 week assessment in the control arm.

The 24 week functional assessment will be identical to the baseline assessment plus administration of all questionnaires described above.

Assessments at 6, 12, 18 and 24 months after completion of the intervention or after completion of the 24 week assessment in the control arm will comprise postal administration of the questionnaires described above.

The primary end-point will be the proportion reaching the recommended physical activity (PA) target of at least 30 minutes of activity of moderate intensity on at least 5 days each week, measured using the CHAMPS, PASE and PHONE_FITT questionnaires, at 12 months after intervention.

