## Objectives

The primary objective is to determine the effect of two evidence based exercise programmes designed for older people, compared with usual care (i.e. with no special interventions to promote physical activity) on the achievement of recommended physical activity targets 12 months after cessation of intervention.

The secondary objectives are to:

(1) determine the health benefits of the programmes to participants starting at various levels of physical activity, particularly the effects on physical and psychological status, health status, health-related quality of life and quality adjusted life years (QALYs).

(2) estimate the costs of the exercise interventions, and possible cost offsets, and to assess the cost-effectiveness of community group exercise, and home-supported exercise compared with each other, and with usual care.

(3) determine the acceptability of the programmes, adherence rates, enabling factors and barriers to future implementation.

(4) compare the time course of responses by participants in terms of exercising at the recommended levels, at 0, 6, 12, 18 and 24 months after cessation of the intervention, between those undergoing the exercise programmes, and those receiving usual care.

(5) determine participants' perceptions of the value of exercise, and the predictors of continued exercise.

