### Blinding

It is difficult for participants to be blind in trials of exercise interventions, and for researchers to be blind to the allocation of participants as they will recruit participants and undertake baseline and follow up assessments. The researchers assessing outcomes are not blinded for pragmatic reasons only; the study is funded to support only enough researchers to carry our recruitment and follow-up simultaneously. However, general practices and their participants, and researchers having contact with practices and participants will not have foreknowledge of the treatment arm allocation of the practice, which will not be disclosed until after all participants within a practice have been recruited. Also, for the statistical analysis of participants' data, the statistician will be blind to the treatment arm allocation of the practices.

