### Statistical methods

Characteristics of participants and practices will be compared descriptively at baseline. Comparisons between treatment arms will be made using random effects models to allow for clustering between practices. Linear regression models will be used for continuous outcome variables, logistic models for binary outcome variables (in particular the primary endpoint, namely attainment of recommended exercise level at 12 months after the intervention), and Poisson or negative binomial models for data on rate of falls. The assumptions for using each model will be checked and analyses adjusted accordingly. All analyses will be undertaken, adjusted (a) for variables used for minimisation (centre, deprivation and practice size), (b) for baseline values of the outcome measure, and (c) for baseline variables which differ to a clinically significant extent between groups. Differential effects of the intervention by age, sex and baseline activity levels will be assessed for the primary outcome measures by adding terms for the interaction between age, sex and baseline activity levels and treatment arm to the regression models.

Multilevel models will be applied to take account of clustering at the practice level (applicable to all arms of the study) and practitioner effects which will apply to differing extents in the OEP arm (due to the effectiveness of different PSIs) and FaME arm (due to the effectiveness of different PMs). Analyses as recommended by Roberts [70] and Walwyn and Roberts [71] (2009) will be applied for this purpose.

While the primary endpoint will be attainment of recommended exercise levels at 12 months, we will investigate the profile of exercise attainment at all time points (0, 6, 12, 18 and 24 months post intervention). We will carry out repeated measures analysis using generalised estimating equations which account for the intra-participant dependency of the repeated measures. In particular we will investigate evidence for differences in effect of the interventions at the different time points.

As the study consists of two intervention arms and one control arm, primary analysis will consist of comparing each intervention group with the control group. No formal adjustment of p-values will be made, since the sample size has been specifically designed to test each intervention separately.

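### Questionnaires at month 0 are tied to an unblinded researcher visit and all later ones are postal, so comparisons of month 0 with later waves mix time with setting (minor, secondary analysis only)

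*Protocol article*

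**What the plan says.** Under Follow-up data collection, the 24-week (month 0) wave is a visit: "The 24 week functional assessment will be identical to the baseline assessment plus administration of all questionnaires described above". The same section says that the assessments at 6, 12, 18 and 24 months "will comprise postal administration of the questionnaires described above". The schedule is the same in all three arms.

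Under Ascertainment of outcomes, researchers carry out the functional assessments: "The following functional assessments will be used by researchers at baseline and at the end of the interventions". The questionnaires, which include the activity measures, are introduced differently: "The following validated tools will be used at baseline, and as self-completion questionnaires at follow-up". No exception is made for 24 weeks.

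Under Blinding: "The researchers assessing outcomes are not blinded for pragmatic reasons only". That section also accepts that participants are hard to blind.

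Secondary objective 4 is to "compare the time course of responses by participants in terms of exercising at the recommended levels, at 0, 6, 12, 18 and 24 months" between the exercise arms and usual care. Statistical methods plans logistic models for binary outcomes and generalised estimating equations over the five waves, and adds that "we will investigate evidence for differences in effect of the interventions at the different time points". It mentions no allowance for the change in how the data are collected.

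**The concern.** Every participant is scheduled for a visit at month 0 and for post at each later wave. At that one step setting is fully determined by time, so the data cannot separate the two.

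The outcome is self-reported activity. At the end of the programme it is reported in connection with a visit by someone who knows the allocation. In the home exercise arm, research staff also introduced the programme. Extra over-reporting in the exercise arms at that visit is plausible, and a common schedule does not cancel a shift that differs by arm.

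The trial asks whether change in activity is sustained. A gap between the month 0 effect and the 6-month effect could be read as loss of benefit, or as late gain, when part of it comes from the change of setting.

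**Working it through.** **1. What is tied to what**

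| Wave | Questionnaires | Unblinded researcher contact |
|---|---|---|
| Month 0 (24 weeks) | given with the functional assessment | yes |
| 6, 12, 18, 24 months | postal | none scheduled |

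One of the five post-baseline waves differs in setting. The other four are alike, and 12 months is postal in every arm.

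**2. The plan's own sample size**

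Inputs from Sample size: 14.6% v 4.9%, two-sided 5%, 90% power, ICC 0.01, 32 participants with data per practice, 30% attrition.

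- Two-proportion formula: 195 per arm without and 215 with continuity correction. The stated 215 is reproduced.
- Design effect: 1 + (32 − 1) × 0.01 = 1.31, and 215 × 1.31 = 281.65, so 282.
- Attrition: 282 / 0.7 = 402.9, so 403.

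The effective size with data is 282 / 1.31 ≈ 215 per arm, which is used below.

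**3. Shift in the exercise arm only**

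Assumptions not in the document: true rates stay at 14.6% v 4.9% at every wave (odds ratio 3.32); within-person correlation ρ = 0.5 between all waves; exercise-arm reporting is inflated by 3, 5 or 8 percentage points at month 0 and nowhere else. The log-odds scale follows the plan's logistic models.

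Contrast: d = log odds ratio at month 0 minus the mean of the four later log odds ratios. Within each arm, with s² = 1/[n p(1 − p)],

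Var = s₀² + s²(1 + 3ρ)/4 − 2ρ s₀ s.

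Worked for 5 points:
- d = logit(0.196) − logit(0.146) = 0.355.
- Exercise arm: s₀² = 0.0295, s² = 0.0373, so Var = 0.0295 + 0.0373 × 0.625 − 0.1718 × 0.1931 = 0.0197.
- Control arm: s² = 0.0998 at all waves, so Var = 0.0998 × (1 + 0.625 − 1) = 0.0624.
- SE = √(0.0197 + 0.0624) = 0.286, and z = 0.355 / 0.286 = 1.24.
- Chance of rejection at 1.96: 24%.

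For a 4-df arm-by-time test the noncentrality is z² in this set-up.

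| Shift at month 0 | Month 0 odds ratio | d | SE | Month 0 v later mean | 4-df test |
|---|---|---|---|---|---|
| 0 | 3.32 | 0 | 0.293 | 5% | 5% |
| 3 points | 4.15 | 0.223 | 0.288 | 12% | 8% |
| 5 points | 4.73 | 0.355 | 0.286 | 24% | 14% |
| 8 points | 5.67 | 0.535 | 0.284 | 47% | 28% |

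With ρ from 0.3 to 0.7, the single-contrast figure for 5 points runs from 18% to 36%.

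**4. Equal over-reporting in both arms**

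Let a share f of true non-achievers report achievement at month 0, so the observed rate is p + (1 − p)f. The rejection column compares month 0 with one later wave, for ρ from 0 to 0.5.

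| f | Observed rates | Month 0 odds ratio | Risk difference | Rejection |
|---|---|---|---|---|
| 0 | 14.6% v 4.9% | 3.32 | 9.7 points | 5% |
| 3% | 17.2% v 7.8% | 2.47 | 9.4 points | 9–14% |
| 5% | 18.9% v 9.7% | 2.18 | 9.2 points | 15–24% |
| 10% | 23.1% v 14.4% | 1.79 | 8.7 points | 28–47% |

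The odds ratio is now lower at month 0 than later, which looks like a rise in effect. The risk difference hardly moves.

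**The case against.** The strongest reply has four parts.

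- **Self-completion is already stated.** Follow-up forms are self-completed with no exception for 24 weeks, and the article uses the word administration for postal forms too. A reader might infer that the two sections contradict each other, or that month 0 is an interview. The text supports neither: the sections can be read together as self-completion at or around a visit. This stands. What is left is a difference of setting and wording loose enough for sites to act on differently.
- **Arms are compared like with like at each wave.** Participants know their arm when they fill in postal forms as well, so arm-related over-reporting can occur throughout. This stands in part. Only the extra due to the visit matters, and its size is unknown.
- **The direction is open.** A reader might infer that a decline will appear by construction and that the month 0 effect is inflated. That needs over-reporting confined to, or larger in, the exercise arms; equal over-reporting lowers the month 0 odds ratio.
- **The outcome at issue is secondary.** Sustained change is judged mainly by each programme against usual care at 12 months, which is postal throughout. The plan only says that it will investigate the profile and does not name month 0 as the reference for decline. This also stands.

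These points reduce the importance. They do not remove the confounding at month 0, because month 0 is explicitly part of the planned comparison.

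**Conclusion.** The point holds in a limited form. In the time-course analysis, contrasts of month 0 with later waves cannot separate time from setting. Contrasts among 6, 12, 18 and 24 months and the 12-month primary analysis are untouched. It is a minor issue in a secondary analysis.

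Under an assumed exercise-arm shift of 3, 5 or 8 points, the chance of a false change in effect is 12%, 24% or 47% for the single contrast, or 8%, 14% or 28% for the 4-df test. A reader testing on the risk-difference scale would get 25%, 55% and 89% for the single contrast. Those figures should not be carried forward, because the plan specifies logistic models for binary outcomes.

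All of these figures rest on an assumed shift, an assumed correlation and a constant true effect. The documents give none of the three, so the figures show sensitivity and do not predict a bias.

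**What to change.** 1. **Follow-up data collection.** State that the 24-week questionnaires are sent ahead and self-completed before the functional assessment, without researcher prompting, in all three arms. This agrees with the self-completion wording under Ascertainment of outcomes.
2. **Statistical methods.** Keep the 0 to 24 month profile, which secondary objective 4 requires. Add an arm-by-time test restricted to the four postal waves (6, 12, 18 and 24 months). Base conclusions about decline after the programme on the result that does not depend on month 0.

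The cost is a few lines of wording, one earlier mailing and one extra analysis. Some packs may be incomplete when the participant attends. Sending forms ahead reduces the difference in setting but does not abolish it, because an unblinded visit still follows. The restricted test cannot describe change from month 0 to month 6, which is why the full profile should stay.
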